## Abstract

**Background:**

There are many avoidable deaths in hospitals because the care team is not well attuned. Training in emergency situations is generally followed on an individual basis. In practice, however, hospital patients are treated by a team composed of various disciplines. To prevent communication errors, it is important to focus the training on the team as a whole, rather than on the individual. Team training appears to be important in contributing toward preventing these errors. Obstetrics lends itself to multidisciplinary team training. It is a field in which nurses, midwives, obstetricians and paediatricians work together and where decisions must be made and actions must be carried out under extreme time pressure.

It is attractive to belief that multidisciplinary team training will reduce the number of errors in obstetrics. The other side of the medal is that many hospitals are buying expensive patient simulators without proper evaluation of the training method. In the Netherlands many hospitals have 1,000 or less annual deliveries. In our small country it might therefore be more cost-effective to train obstetric teams in medical simulation centres with well trained personnel, high fidelity patient simulators, and well defined training programmes.

**Methods/design:**

The aim of the present study is to evaluate the cost-effectiveness of multidisciplinary team training in a medical simulation centre in the Netherlands to reduce the number of medical errors in obstetric emergency situations. We plan a multicentre randomised study with the centre as unit of analysis. Obstetric departments will be randomly assigned to receive multidisciplinary team training in a medical simulation centre or to a control arm without any team training.

The composite measure of poor perinatal and maternal outcome in the non training group was thought to be 15%, on the basis of data obtained from the National Dutch Perinatal Registry and the guidelines of the Dutch Society of Obstetrics and Gynaecology (NVOG). We anticipated that multidisciplinary team training would reduce this risk to 5%. A sample size of 24 centres with a cluster size of each at least 200 deliveries, each 12 centres per group, was needed for 80% power and a 5% type 1 error probability (two-sided). We assumed an Intraclass Correlation Coefficient (ICC) value of maximum 0.08.

The analysis will be performed according to the intention-to-treat principle and stratified for teaching or non-teaching hospitals.

Primary outcome is the number of obstetric complications throughout the first year period after the intervention. If multidisciplinary team training appears to be effective a cost-effective analysis will be performed.

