### Hypothesis

Multiprofessional, obstetric emergency training in a medical simulation centre with high fidelity patient simulators and well educated instructors leads to a reduction of perinatal and maternal morbidity.

Questions to be answered:

1. Does medical simulation of obstetric teams in a medical simulation centre reduce the number of errors in acute situations?

2. What is the influence of medical simulation trainings of obstetric teams in a medical simulation centre on the perinatal outcome?

3. What are the costs of medical simulation trainings of obstetric teams in a medical simulation centre?

4. What is the cost-effectiveness of medical simulation trainings of obstetric teams in a medical simulation centre?

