### Economic evaluation

The trial results will be incorporated in a cost-effectiveness analysis to compare the costs and effects of multidisciplinary team training in a medical simulation centre (experimental strategy) versus no such training (reference strategy).

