The costs of the implementation intervention will be calculated separately. We will calculate the costs of patient counselling, the costs of education of health care professional as well as the costs of distribution of patient leaflets. The sensitivity of costs and health outcomes for various parameters is tested in sensitivity analysis and visualised in Incremental Cost-Effectiveness Ratio (ICER) graphs and acceptability curves. When the study would show that multidisciplinary team training would be effective, the primary economic analysis will be a cost-effectiveness analysis. If multidisciplinary team training would appear to reduce complications, we will calculate the costs per prevented complication. No power calculations will be performed for the economic evaluation study as it is embedded in a randomised controlled trial.

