#### Data analysis

Our primary (base-case analyses) will be performed according to the intention-to-treat principle and stratified for teaching or non-teaching hospital. A baseline analysis will be performed to examine the comparability of groups at baseline for both costs and outcomes. To investigate whether data are normally distributed a Kolmogorov-Smirnov test will be performed. Despite the usual skewness in the distribution of costs, the arithmetic means will be generally considered the most appropriate measures to describe cost data. Therefore arithmetic means (and standard deviations) will be presented. In case of skewness of the cost data, non-parametric bootstrapping will be used to test for statistical differences in costs between the intervention and control group. Non-parametric bootstrapping is a method based on random sampling with replacement based on individual data of the participants. The bootstrap replications will be used to calculate 95% confidence intervals around the costs (95% CI), based on the 2.5th and 97.5th percentiles. If cost data are distributed normally, t-tests will be used. The Incremental Cost-Effectiveness Ratio (ICER) will be determined on the basis of incremental costs and effects of team training compared with non-team training. The cost-effectiveness ratio will be stated in terms of costs per outcome rate, the cost-utility ratio will focus on the net cost per QALY (Quality Adjusted Life Year) gained. The robustness of the ICER will be checked by non-parametric bootstrapping (1000 times). Bootstrap simulations will also be conducted in order to quantify the uncertainty around the ICER, yielding information about the joint distribution of cost and effect differences. The bootstrapped cost-effectiveness ratios will be subsequently plotted in a cost-effectiveness plane, in which the vertical line reflects the difference in costs and the horizontal line reflects the difference in effectiveness. The choice of treatment depends on the maximum amount of money that society is prepared to pay for a gain in effectiveness, which is called the ceiling ratio. Therefore, the bootstrapped ICERs will also be depicted in a cost-effectiveness acceptability curve showing the probability that team training is cost-effective using a range of ceiling ratios.

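### The abstract makes the cost-effectiveness analysis depend on apparent effectiveness, which conflicts with the study's stated aim, its question 4 and the unconditional plans in the body

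*Protocol article*

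**What the plan says.** The protocol article gives two rules for the economic analysis.

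**Without a condition**
- Abstract, Methods/design, opening sentence: "The aim of the present study is to evaluate the cost-effectiveness of multidisciplinary team training in a medical simulation centre".
- Hypothesis, question 4: "What is the cost-effectiveness of medical simulation trainings of obstetric teams in a medical simulation centre".
- Economic evaluation: "The trial results will be incorporated in a cost-effectiveness analysis to compare the costs and effects of multidisciplinary team training".
- Data analysis: the ICER is bootstrapped, "yielding information about the joint distribution of cost and effect differences", and then shown on a cost-effectiveness plane and as an acceptability curve. No condition is attached.

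**With a condition**
- Abstract, Methods/design, closing sentence: "If multidisciplinary team training appears to be effective a cost-effective analysis will be performed".
- Cost analysis: "When the study would show that multidisciplinary team training would be effective, the primary economic analysis will be a cost-effectiveness analysis".
- Cost analysis, for the single ratio: "If multidisciplinary team training would appear to reduce complications, we will calculate the costs per prevented complication".

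The article does not say whether apparent effectiveness means a significant test or a favourable point estimate. It does not say which economic analysis follows if the condition fails.

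**The concern.** The analysis that answers the study's own aim is made to wait on a different result. Followed as the abstract words it, the plan could complete a trial, with resource use collected in every centre, and report no cost-effectiveness result. The Background justifies the trial by hospitals adopting costly simulators without evaluation of effectiveness or cost. In that setting an uncertain or null effect set beside its cost is useful to decision makers, and the condition would withhold exactly that.

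The condition also sits badly with the method chosen. A joint bootstrap, a plane and an acceptability curve over a range of ceiling ratios already carry uncertainty about the effect, so they need no prior filter on it. If the filter is a significance test, the ratios that get reported also come from trials whose effect estimates are, on average, too large.

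**Working it through.** **Inputs from the Sample size section:** 15% versus 5%; 12 centres per group; at least 200 deliveries per centre, later 1,000; ICC at most 0.08; two-sided 5%; 80% power. The 7.5% rate and the lower ICCs used below are assumptions.

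**1. The plan's own figure.** The two-proportion formula with pooled variance under the null gives [1.960×√(2×0.10×0.90) + 0.842×√(0.1275+0.0475)]² / 0.10² = 140.1, so 141 per arm. The design effect is 1 + 199×0.08 = 16.92. Centres per arm: 141×16.92/200 = 11.93, so 12. Power with 12 per arm is 80.5%. The stated 24 centres reproduce.

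**2. How often a p<0.05 condition blocks the analysis.** With d the true risk difference, SE = √{[p1(1−p1) + p2(1−p2)] × DE / (12m)} and P(pass) = 1 − Φ(1.96 − d/SE).

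- 15% v 5%, m=200, ICC 0.08: SE = √(0.175×16.92/2,400) = 0.0351; d/SE = 2.85; P(pass) = 0.81. Blocked: 19%.
- 15% v 5%, m=1,000, ICC 0.08: DE = 80.92; SE = √(0.175×80.92/12,000) = 0.0344; d/SE = 2.91; P(pass) = 0.83. Blocked: 17%.
- Assumed 15% v 7.5%, m=1,000, ICC 0.08: SE = √(0.1969×80.92/12,000) = 0.0364; d/SE = 2.06; P(pass) = 0.54. Blocked: 46%.
- The same assumed effect with ICC 0.02: DE = 20.98; d/SE = 4.04; P(pass) = 0.98. Blocked: 2%. With 15% v 5% and ICC 0.02, the blocked share is below 0.1%.

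A t-test on 22 degrees of freedom has power 77.7% (m=200) or 79.4% (m=1,000) at the design point, so the blocked share would be 21 to 22%.

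**3. Average overstatement among trials that pass.** With a = 1.96 − d/SE, the mean reported effect divided by the true effect is 1 + (SE/d) × φ(a)/[1 − Φ(a)].

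- 15% v 5%, m=200, ICC 0.08: a = −0.887; 1 + (1/2.847) × 0.2692/0.8125 = 1.12.
- 15% v 5%, m=1,000, ICC 0.08: a = −0.951; 1 + (1/2.911) × 0.2538/0.8292 = 1.11.
- Assumed 15% v 7.5%, m=1,000, ICC 0.08: a = −0.098; 1 + (1/2.058) × 0.3970/0.5392 = 1.36.
- Condition taken as an estimate above zero, design point: P(pass) = 0.998 and the ratio is 1.00.

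With the incremental cost held fixed, a cost divided by the mean reported effect is about 10% too low at the design point (1/1.12 = 0.90). The mean of the reported ratios themselves, E[d/D | pass] with D the estimated risk difference, is 0.95 to 0.96 there, so 4 to 5% too low.

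**The case against.** The strongest reply is that this is mainly loose wording. The Economic evaluation and Data analysis sections plan the analysis outright. The conditional sentence in Cost analysis can be read as naming which economic analysis is primary once an effect is shown, not whether one is done. That leaves one abstract sentence as the explicit condition. This stands to the extent that the plan is inconsistent, not conditional throughout. It does not remove the conflict, because the abstract's sentence stands beside the aim it would leave unanswered.

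Three stronger readings are tempting, and the documents do not support them.

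- A reader might infer that the costs question (question 3) would also go unanswered. It would not. Resource use is measured and valued, training costs are calculated separately, and cost differences are tested, all without a condition.
- A reader might infer that the reported cost per prevented complication will be too favourable. The condition does not alter the estimate from a given data set. The overstatement is an average over trials that pass a significance test, and the article does not say that such a test is meant.
- A reader might take 46% and 1.36 as the size of the problem. They rest on an assumed 7.5%. The roughly 50% reductions cited in the Background concern low Apgar scores and hypoxic ischaemic encephalopathy, not this composite. They also use the ICC at its stated maximum.

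It is also fair to say that the condition on cost per prevented complication is sensible in itself, since that ratio has no such meaning when no complications are prevented.

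**Conclusion.** The point holds as an internal contradiction with a real consequence: following the abstract could leave the stated aim and question 4 unanswered. Its size depends on an undefined criterion. Read as two-sided p<0.05, the analysis would be missing in about 17 to 19% of trials at the design assumptions. It would be missing more often if the true effect is smaller, and almost never at the planned effect if the ICC is well below 0.08. The average overstatement of the effect in reported ratios is secondary: about 11 to 12% at the design point on that reading, more with lower power, and essentially none there if a favourable estimate suffices. These figures use a normal approximation with equal cluster sizes. The contradiction does not depend on them.

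**What to change.** Reconcile the abstract and the Cost analysis section with the Hypothesis, Economic evaluation and Data analysis sections. State that the cost-effectiveness analysis (incremental costs and effects, joint bootstrap, plane and acceptability curve) will be done and reported whatever the result on the primary outcome. Replace the abstract's conditional sentence accordingly, and reword the Cost analysis sentence so that the choice of primary economic analysis does not depend on the effect result.

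The sentence on cost per prevented complication can stay. Add that the plane and the acceptability curve cover the case where complications are not reduced.

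The cost is analysis time only: resource use is already to be collected prospectively in all participating centres, so no further data are needed.

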**Discussion:**

If multidisciplinary team training appears to be cost-effective, this training should be implemented in extra training for gynaecologists.

**Trial Registration:**

The protocol is registered in the clinical trial register number NTR1859

The development of patient simulators began in anaesthesiology at the end of the 1980s [6-8]. The first simulators consisted of relatively simple interactive software programs that were played on a computer screen. Later, these software programs were integrated in real-life dummies that were operated by an instructor. The most advanced dummies are model-driven. These high fidelity patient simulators can be fully programmed to simulate a certain acute disorder. The scenarios can be applied to the specific target group. Participants can be tested on their individual clinical skills and competency to work together under pressure as a team. What are the advantages of team training of health care professionals in a medical simulation centre?

- Training of health care teams in emergency situations promotes cooperation and reduces the number of communication errors [9,10];

- Training in a medical simulation centre offers the opportunity to train rare emergency scenarios under standardised conditions and give targeted feedback on functioning as individual and team;

- Acceptance of team training results in a culture that devotes more attention to patient safety [11].

Against these advantages there are also some disadvantages:

- The costs of introducing simulation training strongly depend on the objective of the simulation, the intended target group and the applied technology. Practicing on personal computers and low-fidelity phantoms is relatively inexpensive. Investment in high-fidelity patient simulators is substantial, but cheaper than practicing on laboratory animals [12];

- New training curricula with expensive patient simulators have been developed for obstetric teams and some have already been introduced in Dutch hospitals without proper evaluation of effectiveness and costs of the training. A survey among all Dutch departments of obstetrics in January 2008 revealed that 90% of the responders had the intention to start team training with patient simulators without any clear description of the content of the training;

- Local training of obstetrical teams might be even effective as training in a simulation centre [13]. However, that study was performed in six hospitals in the United Kingdom with delivery rates ranging from 2,500 to 4,600 per annum. Dutch obstetrical departments are relatively small. In the Netherlands delivery rates range from 500 to 2,500 per year. Many hospitals have less than 1,000 deliveries per annum. Therefore it will be complicated to find enough well educated instructors for local hospital training and reach a high level of training which might lead to less effectiveness.

### Relevance

The value of team training in a simulated environment has been recognised in the USA. There are hundreds of medical simulation centres with high fidelity patient simulators. The Riverside Methodist Hospital in Ohio, a highly advanced medical simulation centre, was recently opened. This centre includes three departments:

- A virtual care unit, consisting of an operating room, a trauma room, an intensive care, a surgery room and an emergency room;

- A skills laboratory, consisting of laboratories to learn laparoscopic skills, suturing, catheterisation, clinical skills and patient examination rooms;

- Multimedia conference areas for interactive learning.

Medical simulation centres have also been put in use in the UK, Germany and Scandinavia. The Society for Simulation in Healthcare (SSH) in the United States and the Society in Europe for Simulation Applied to Medicine (SESAM) are growing exponentially and work well together. The Máxima Medical Centre (MMC) in Eindhoven-Veldhoven has taken the initiative in the Netherlands in applying team training using practical medical simulation. Medical simulation is an important component of the 10 years research plan of the collaboration on scientific research between Máxima Medical Centre and the University of Technology Eindhoven (TU/e). In the Medical Education and Simulation Centre (medsim) in Eindhoven all multidisciplinary teams that are engaged in emergency care are trained in a simulation setting that resembles reality as closely as possible. Commercially available high fidelity patient simulators are used. In cooperation with the University of Technology Eindhoven and the University of Porto, work is also being performed on improving simulators and developing new high fidelity patient simulators in the field of neonatology and obstetrics.

For the technological improvement of birthing simulations a subsidy has been recently obtained from the Stimulus foundation (European foundation for regional development) by MMC in association with the University of Technology Eindhoven and the European Design Centre. The development of programs for the medical education and simulation centre (medsim) is made possible by support of Máxima Medical Centre and Dutch health insurance companies VGZ and CZ.

Initially, a start was made with a study in the delivery rooms by [name] et al. in 2006. Six emergency scenarios were used for the study. The teams were comprised of a gynaecologist or a gynaecology resident, a midwife and a nurse or assistant midwife. All instructors and facilitators received special training in crew resource management. Special childbirth simulators are used. The Noelle™ (Gaumard, Miami Florida) maternal childbirth simulator is an interactive manikin that can simulate diverse obstetric emergency scenarios guided by instructors. Baby Hal™ (Gaumard, Miami Florida) is an interactive wireless newborn simulator, and Prompt Birthing Trainer™ (Limbs & Things, Bristol UK) is an interactive birthing simulator for shoulder dystocia with force feedback. Aside from knowledge and skills, cooperation and communication between the various team members is monitored for the assessment. Standardised questionnaires were used for the evaluations. The results showed that all participants were positive about the team training. Individual knowledge, skills, cooperation and communication between the team members improved. The results confirmed the positive experience of other researchers [9,13].

In a large British retrospective cohort study it has been shown that team training in obstetric emergencies results in a reduction of poor perinatal outcome [3]. In a large study where 19,460 neonates were involved, the introduction of obstetric emergencies training courses resulted in a reduction of 49% (from 86.6 to 44.6 per 10,000 births) of neonates born with low Apgar scores (5-minutes <6) and reduction of 50% of infants with hypoxic ischemic encephalopathy (from 27.3 to 13.6 per 10,000 births) [3].

## Methods/Design

The proposed research concerns a multicentre randomised controlled trial of obstetric departments in the Netherlands. These obstetric departments will be randomly assigned to receive multidisciplinary team training in a medical simulation centre or to a control arm without any team training.

### Recruitment

We invited several teaching and non-teaching hospitals in the Netherlands to participate in this randomised study. We excluded hospitals which already have frequently multidisciplinary team training for its care workers, as defined by more than once every year. Randomisation will be performed through a database which is hosted at the Academic Medical Centre (AMC) in Amsterdam. Randomisation will be 1:1 for intervention and control group and it will be stratified for teaching or non-teaching hospital because we expect differences in outcomes in teaching and non-teaching hospitals.

### Hypothesis

Multiprofessional, obstetric emergency training in a medical simulation centre with high fidelity patient simulators and well educated instructors leads to a reduction of perinatal and maternal morbidity.

Questions to be answered:

1. Does medical simulation of obstetric teams in a medical simulation centre reduce the number of errors in acute situations?

2. What is the influence of medical simulation trainings of obstetric teams in a medical simulation centre on the perinatal outcome?

3. What are the costs of medical simulation trainings of obstetric teams in a medical simulation centre?

4. What is the cost-effectiveness of medical simulation trainings of obstetric teams in a medical simulation centre?

### Intervention

The intervention group will have multidisciplinary team training in a medical simulation centre. These team trainings are given by specially trained instructors and facilitators (gynaecologists, communication experts and psychologists). All instructors and facilitators are trained in crew resource management. To make the context of the training lifelike these take place in an entirely reconstructed delivery room. State of the art high fidelity patient simulators will be used. Fetal distress (including a cardiotocogram training program), postpartum haemorrhage, eclampsia, umbilical cord prolapse and shoulder dystocia scenario's are practiced on the birthing simulator Noelle™ (Gaumard Miami, Florida) and Prompt Birthing Trainer™ (Limbs & Things, Bristol), perimortem caesarean section on the emergency care simulator ECS™ (Meti, Sarasota, Florida), and resuscitation of asphyxiated infants on the neonatal simulator (Baby Hal™, Gaumard, Miami, Florida). For hospitals randomised to receive the team training, the interventions will be planned. Depending on the size of the department it concerns 3 up to 10 sessions. A team will consist of a group of about 6 care workers in means of one gynaecologist and one or more residents, midwifes and nurses. For one hospital all sessions are carried out in a timeframe with a maximum of 4 weeks. This means that several teams of the same hospital will be trained. In the real life setting in their own hospitals there will be a different composition of team members but every delivery room care worker has been trained in the simulation centre.

The team training will take place at the medical education and simulation centre in Eindhoven (medsim) where the following scenarios will be trained: Fetal distress including CTG analysis, shoulder dystocia, severe postpartum haemorrhage, eclampsia, umbilical cord prolapse and perimortem caesarean section. The scenarios are based on national and international accepted guidelines by NVOG (The Dutch Society for Obstetrics and Gynaecology) and MOET (Managing Obstetric Emergencies & Trauma). Each scenario starts with a briefing session in a simulated emergency room of 10 minutes in which the case is presented by means of a video play on a wide screen. The team will then move to the simulated delivery room. In the delivery room they have to treat the patient. The patient is a an advanced interactive birthing simulator. The facilitator gives wireless instructions to the robot from the control room. The whole session is videotaped. The simulation session will take 20 minutes. Then the team will move to the briefing room. The facilitators will give feedback on teamwork and skills using video recording. The debriefing session will take about 30 minutes.

There will be an effect measurement after six months following the team training, by in-situ training in all participating hospitals, including the control arm.

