### Outcome measures

Primary outcome is the number of obstetric complications throughout the first year after the intervention. Obstetric complications will be defined as the number of neonates with perinatal asphyxia (Apgar score 5-minutes <7 and/or arterial umbilical pH < 7.05, hypoxic ischemic encephalopathy (HIE), number of newborns with damage caused by shoulder dystocia (e.g. lesion of brachial plexus, clavicle fracture), number of women with eclampsia, number of women with severe post partum haemorrhage (blood transfusion >4 packed cells, embolisation, hysterectomy). Shoulder dystocia is hereby described as every additional manoeuvre for successful alleviation.

Sub analysis will be performed to identify possible changes in subgroups. These groups concern term infants (gestation over 37 weeks), singleton pregnancies and cephalic presentation at birth.

Secondary outcomes are perinatal and maternal mortality, divided by causes of death.

These complications will be obtained from the regular obstetric recordings after informed consent from the participating hospitals (with exception of damage due to shoulder dystocia and severe postpartum haemorrhage, these data will be registered separately). Before the start of the project indicators will be developed to evaluate patient safety, teamwork and human factors. These indicators will be registered in a subgroup of the participating hospitals. This group will consist of 100 obstetric complications equally distributed in the intervention and control group.

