### Statistics

#### Sample size

The composite measure of poor perinatal and maternal outcome in the non training group was thought to be 15%, on the basis of data obtained from the National Dutch Perinatal Registry and the guidelines of the Dutch Society of Obstetrics and Gynaecology (NVOG). We anticipated that multidisciplinary team training would reduce this risk to 5%. A sample size of 24 centres with a cluster size of each at least 200 deliveries, each 12 centres per group, was needed for 80% power and a 5% type 1 error probability (two-sided). We assumed an Intraclass Correlation Coefficient (ICC) value with a maximum of 0.08. Because there is an uncertainty about the complication rate and perhaps this is lower than expected a sample size of 1000 deliveries per hospital was taken. In conclusion we will try to randomise 24 obstetric departments in the Netherlands with an one year follow-up.

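### In-situ training of control hospitals at month 6 conflicts with a comparator of no team training and falls midway through the one-year primary outcome window

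*Protocol article*

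**What the plan says.** Under Methods/Design, departments are "randomly assigned to receive multidisciplinary team training in a medical simulation centre or to a control arm without any team training". The abstract describes the control arm in the same way.

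The last sentence of the Intervention section adds: "There will be an effect measurement after six months following the team training, by in-situ training in all participating hospitals, including the control arm".

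Under Outcome measures: "Primary outcome is the number of obstetric complications throughout the first year after the intervention". The Sample size section agrees on the length of follow-up: "we will try to randomise 24 obstetric departments in the Netherlands with an one year follow-up".

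Two other statements bear on the point. On eligibility, Recruitment says: "We excluded hospitals which already have frequently multidisciplinary team training for its care workers, as defined by more than once every year". On whether training outside a simulation centre can work, the Background concedes: "Local training of obstetrical teams might be even effective as training in a simulation centre". It then gives reasons to doubt this for small Dutch units.

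**The concern.** The comparator, the timing of the in-situ session and the outcome window do not fit together. A control arm with no team training cannot also receive in-situ training, and month 6 is the midpoint of the period over which the primary outcome is counted. The article does not say that the session is assessment without teaching, and it does not limit the primary outcome to the months before the session.

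The interpretation of the primary result is at stake. From month 7 the comparison is simulation-centre training plus an in-situ session against an in-situ session alone. If untrained teams learn more from that session than teams already trained, the observed difference over the year understates the effect of centre training against none. Analysis cannot remove an exposure that the design itself gave to the controls. The sample size makes no allowance for it either: it assumes an untrained rate of 15% for the whole year.

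**Working it through.** **Inputs from the article (Sample size):** control rate 15%, intervention rate 5%, 12 centres per arm, at least 200 deliveries per centre and later 1,000, ICC at most 0.08, two-sided 5%, power 80%.

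**The plan's own figure.** With pooled variance and no continuity correction, 15% versus 5% needs 141 per arm under individual randomisation. The design effect is 1 + (200 − 1) × 0.08 = 16.92. Then 141 × 16.92 / 200 = 11.93, which rounds up to 12 centres per arm. The stated 24 centres reproduce, so there is no arithmetic error.

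**Slack.** At 1,000 deliveries the design effect is 1 + 999 × 0.08 = 80.92, and 141 × 80.92 / 1,000 = 11.41 centres per arm. Going from 200 to 1,000 deliveries therefore saves about half a centre per arm. The larger hospitals give almost no reserve against dilution of the effect.

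**Illustration of dilution.** None of the following assumptions is in the article. Deliveries are spread evenly over the year; the month-6 clock is the same in both arms; and from month 7 the session gives controls a fraction g of the planned 10-point effect.

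- Control average over the year: 0.5 × 15% + 0.5 × (15% − g × 10%) = 15% − g × 5%.
- Effective size per arm: 12 × 1,000 / 80.92 = 148.3.
- SE = √{[p₁(1 − p₁) + p₂(1 − p₂)] / 148.3} (unpooled); power = Φ(|p₁ − p₂| / SE − 1.96).

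Without dilution: SE = √(0.175 / 148.3) = 0.0344; 0.10 / 0.0344 = 2.91; power = Φ(0.95) = 83%.

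The result depends on what the same session does in the intervention hospitals, so three cases are needed.

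| Benefit in the intervention arm | g = 0.25: rates | Power | g = 0.5: rates | Power |
|---|---|---|---|---|
| None | 13.75% vs 5% | 74% | 12.5% vs 5% | 64% |
| Same relative reduction | 13.75% vs 4.58% | 79% | 12.5% vs 4.17% | 75% |
| Same absolute reduction | 13.75% vs 3.75% | 87% | 12.5% vs 2.5% | 91% |

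In the second row the control average is multiplied by 13.75/15 = 0.917 or 12.5/15 = 0.833, and the 5% is multiplied by the same factor. In the third row the difference stays at 10 points; power rises only because the variances are smaller.

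Worked example for 12.5% versus 5%: SE = √[(0.1094 + 0.0475) / 148.3] = 0.0325; 0.075 / 0.0325 = 2.31; power = Φ(0.35) = 64%.

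**The case against.** The strongest reply is that the article presents the month-6 event as a measurement, with in-situ training only as its vehicle. The intervention under test is far larger: 3 to 10 sessions per department, specially trained instructors, a reconstructed delivery room, and every delivery-room worker trained. The debriefing of about 30 minutes is described for the simulation-centre sessions, not for month 6. A condensed article may leave the operational detail to the full protocol. Both arms receive the session, randomisation is intact, and months 0 to 6 are untouched. The economic evaluation uses no such training as its reference strategy, which controls still satisfy if it means no simulation-centre training.

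Much of this stands, and it rules out several stronger readings:

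- A reader might infer that the bias is certainly toward no effect. The table shows that this depends on how the session acts in already trained hospitals.
- A reader might take the extreme case, in which controls gain the full effect from month 7 (10% versus 5%, power 38%), as a forecast. It would need one session of unstated coverage to equal the whole programme and to add nothing in trained hospitals. The Background doubts that local training in small Dutch units would be as effective.
- A reader might conclude that a null result would be uninterpretable. It would still be a randomised comparison of centre training against no centre training, with a session common to both arms at month 6.
- A reader might take the eligibility rule as proof that controls are trained during follow-up. It excludes only hospitals whose prior training was frequent, "as defined by more than once every year". It says who may enter, not what controls then receive, and randomisation should balance prior training in expectation.

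The reply does not remove the conflict. The article itself calls the session training, places it in control hospitals inside the outcome window, and defines those hospitals as having none. That is a stated design feature, not a detail left out.

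**Conclusion.** The point holds as an internal contradiction with a probable, unquantified cost. The definition of the control arm and the month-6 in-situ training cannot both be true, and about half of the control-arm outcome period follows that session. The full-year contrast is therefore not training versus none. Dilution toward no effect is likely, because untrained teams plausibly gain more than trained ones, but it is not certain.

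No single power figure should be quoted as the consequence. If controls gain a quarter to a half of the planned effect, power lies between 64% and 79%, against 83% undiluted, across the first two rows of the table; under an equal absolute benefit the contrast is not reduced. All of this rests on the article's 15%, 5% and ICC of 0.08 and on assumed values of g. Severity: should-fix.

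**What to change.** 1. Hold the in-situ measurement in all hospitals after the 12-month outcome window has closed. If month 6 is kept, run it in control hospitals as assessment only, with no teaching, debriefing or feedback until month 12, and say so in the Intervention section.
2. If month 6 is kept, pre-specify a supportive analysis of the primary outcome restricted to months 0 to 6.
3. Reword the comparator as no simulation-centre training, since hospitals that train up to once a year are eligible, and record local team training in both arms during follow-up.

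The cost is one rescheduled visit or a restricted session format, a wording change and a short training log. The downside is that the teamwork effect is measured at 12 rather than 6 months or, if month 6 is kept, that control teams get their feedback later. The months 0 to 6 analysis covers about half the deliveries, but at an ICC of 0.08 the number of hospitals drives precision far more than the number of deliveries in each.
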